### Utility analysis

Over the 26-week period, the proportion of time with sensor glucose will be tabulated for each treatment arm, in addition to the proportion of time with closed-loop system active in the closed-loop arm.

### Safety analysis

For each of the following safety outcomes, mean±SD or summary statistics appropriate to the distribution will be tabulated by treatment group:

Number of severe hypoglycaemia events.Number of participants with any severe hypoglycaemia event.Number of adverse events per participant.Number of serious adverse events per participant.

All of the above safety outcomes will be tabulated for all participants (including dropouts and withdrawals), regardless of whether CGM data are available and irrespective of whether closedloop was operational. All serious adverse events will be listed for the entire study duration.

### Human factor evaluation

#### Questionnaires

Descriptive tabulations of questionnaires will be carried out, and scores will be calculated using the provided scaling and scoring tools as appropriate. The between-group difference of each score will be assessed using a linear mixed model, adjusting for the corresponding score at baseline, age and clinical centre.

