### Randomisation

At the end of the run-in period (2–3 weeks after visit 1), participants’ CGM data will be reviewed. A minimum of 10 days of data recorded, and less than 80% time in target glucose range, will be needed to proceed with randomisation. Eligible participants will be randomised in a 1:1 ratio to the use of HCL or to standard insulin therapy with CGM for 26 weeks. Randomisation will be done using a centrally administered web-based randomisation sequence with a permuted block design (block sizes 2 and 4) and will be stratified by site, age (≤30 years/>30 years) and baseline time in target glucose range (≤65%/>65%). Participants and investigators will not be masked to the intervention used during each period because of the nature of the interventions.

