#### Primary outcome analysis

The primary analysis will evaluate the between-group difference in the proportion of time spent in the target glucose range of 3.9 and 10.0 mmol/L based on CGM levels during the 26-week intervention period.

The values will be compared using a linear mixed model; the dependent variable is the primary endpoint and the independent variable is treatment allocation, adjusting for baseline time in target glucose range, age and clinical centre. A 95% CI will be reported for the difference between the interventions based on the linear mixed model. Residual values will be examined for an approximate normal distribution. If values are highly skewed, then a transformation or robust statistical method will be used instead. A 5% significance level will be used to declare statistical significance for the primary comparison. A two-sided p value will be reported. The primary analysis will be a single statistical comparison of a single outcome measure.

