### Sample size calculation

The primary analysis will evaluate the between-group difference in the proportion of time in target glucose range of 3.9 and 10.0 mmol/L based on sensor glucose from initiation of the treatment arm to 26 weeks. Data from four studies were considered when preparing the sample size calculations for this study.^18^,^21^ For a clinically important 5.0 percentage point absolute mean difference in time with glucose in target range,^22^ an SD of 8.1, 90% power, two-sided t-test at 5% significance level and 1:1 randomisation, total sample size is estimated to be 114 participants (57 per treatment group). Allowing for 10% loss to follow-up (5–8% in previous studies), we aim to randomise a total of 128 participants (64 per treatment group).

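### The questionnaire model leaves out baseline time in range, a stratification factor that the primary model keeps; any cost is conservative and probably small, and adding the term is free

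*Protocol article*

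**What the plan says.** Three places in the protocol article bear on this.

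- **Randomisation.** Allocation is "stratified by site, age (≤30 years/>30 years) and baseline time in target glucose range (≤65%/>65" per cent, using a "permuted block design (block sizes 2 and 4").
- **Primary outcome analysis.** The linear mixed model for time in range is fitted "adjusting for baseline time in target glucose range, age and clinical centre". All three stratification factors are in it.
- **Human factor evaluation, Questionnaires.** After descriptive tabulation, the between-group difference in each score is assessed with a linear mixed model "adjusting for the corresponding score at baseline, age and clinical centre". Site and age are kept; baseline time in range is not listed.

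Table 3 shows which instruments this touches. PAID, Hypoglycaemia Confidence, EQ-5D-3L and CFQ-R are collected in both arms at baseline, 3 and 6 months. INSPIRE (at follow-up) and the closed-loop experience questionnaire are collected in the closed-loop arm only, so no between-group follow-up comparison arises for them.

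**The concern.** When allocation is balanced on a factor by design and that factor predicts the outcome, leaving it out of the model keeps its variance in the residual. The model then reports a standard error larger than the real sampling error of the treatment difference: intervals are wider than necessary and tests reject less often than their nominal level. To the extent that balance is imperfect, some real precision is lost too.

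The article fixes the covariate list for the questionnaires, so this is a stated choice and not a detail left open. The list accepts the principle of adjusting for design factors, since it keeps two of the three, and no reason is given for dropping the third. What is at stake is the precision of the patient-reported comparisons, which have no power calculation of their own.

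**Working it through.** **The plan's own figure.** The sample size rests on a "clinically important 5.0 percentage point absolute mean difference in time with glucose in target range", an SD of 8.1 and "90% power, two-sided t-test at 5% significance level and 1:1 randomisation". The normal approximation gives 2 × (1.960 + 1.282)² × 8.1² / 5² = 55.2, so 56 per arm. The exact t-test gives 56.13, so 57 per arm and 114 in total, as stated. Allowing for 10% loss, 57 / 0.9 = 63.3, so 64 per arm and 128 in total, as stated. Both figures reproduce, and neither depends on the questionnaire model.

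**Inputs for the questionnaires.** The article gives no SD, effect size or power for any questionnaire. It also gives no correlation between baseline time in range and the scores. Let r be the partial correlation of baseline time in range with the follow-up score, given baseline score, age and centre. It is assumed to lie between 0 and 0.5.

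**Formulas**, assuming the factor is fully balanced between arms:

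- Ratio of model standard errors, factor omitted to factor included: k = 1/√(1 − r²).
- Power with the factor omitted: Φ(1.960 + z − 1.960k), where z is 0.842 or 1.282 if the model with the factor has 80% or 90% power.
- Type I error with the factor omitted: 2 × [1 − Φ(1.960k)].

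Example at r = 0.2: k = 1/√0.96 = 1.021. From 80%, power is Φ(2.802 − 2.000) = Φ(0.801) = 78.9%. Type I error is 2 × [1 − Φ(2.000)] = 4.6%.

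| Assumed r | k | Power, from 80% | Power, from 90% | Type I error |
|---|---|---|---|---|
| 0 | 1.000 | 80.0% | 90.0% | 5.0% |
| 0.1 | 1.005 | 79.7% | 89.8% | 4.9% |
| 0.2 | 1.021 | 78.9% | 89.3% | 4.6% |
| 0.3 | 1.048 | 77.3% | 88.2% | 4.0% |
| 0.5 | 1.155 | 70.5% | 83.6% | 2.4% |

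**Cross-check by simulation.** Settings: 114 participants, 8 sites (assumed), blocks of 2 and 4 within site by age by time-in-range strata, baseline score in both models, fixed-effect regression in place of the mixed model, 4,000 runs per setting. The standard-error ratios were 0.997, 1.002, 1.018, 1.046 and 1.154 at r = 0, 0.1, 0.2, 0.3 and 0.5, in line with the formula.

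Simulated power with the factor omitted and included was 79.8% and 80.9% at r = 0.2, 80.2% and 83.5% at r = 0.3, and 82.9% and 90.8% at r = 0.5.

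The simulated type I error with the factor omitted was 5.2% at r = 0.2 and at r = 0.3, and 4.4% at r = 0.5 (Monte Carlo standard error √(0.05 × 0.95 / 4000) = 0.3 points). It falls less than the formula predicts. Eight sites by two by two make 32 strata for 114 participants, about 3.6 each, so many blocks stay incomplete, and stratifying at a cut-point balances a continuous measure only in part. Some of the wider standard error is therefore real loss of precision and not pure conservatism. The formula's type I figures are the limit under full balance.

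**The case against.** The strongest case on the other side has four parts.

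1. **The loss is conditional.** It exists only if baseline time in range adds information beyond the baseline score, which is usually the best predictor of a later score. At r = 0 the extra term widens the standard error very slightly (simulated ratio 0.997). This stands, and it limits the point.
2. **The questionnaire model follows a sensible template.** In the primary model, baseline time in range is also the baseline value of the outcome. The questionnaire model keeps the same shape: outcome at baseline, age, centre. This explains how the omission may have come about. It does not restore the third factor, because here the baseline outcome and the stratification factor are two different variables.
3. **No powered result depends on it.** The questionnaires are not among the listed key or other secondary endpoints, no significance level is set for them, and the Introduction describes the work on quality of life as exploratory. This stands.
4. **Any miscalibration is on the safe side.** This stands too.

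A reader might infer that the patient-reported results will definitely have standard errors that are too wide and will lose material power. The article does not support that. A 15% wider standard error and a power loss of 6 to 10 points need r near 0.5 on top of the baseline score, and nothing in the article points to a value that large.

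**Conclusion.** The omission holds as a matter of text: the questionnaire model drops a factor that the trial randomises by and that its primary model keeps. The consequence is conditional and probably minor. With r assumed, the standard error is about 2% wider with about 1 point of power lost at 0.2, about 5% and 2 to 3 points at 0.3, and nothing at 0. These figures assume balance on the factor; the 8 sites and the fixed-effect regression enter only the cross-check.

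The treatment difference is not biased and false positives do not increase. A reader might also infer that the headline result or the trial's size is in doubt. Neither is: the primary model contains all three factors, and 114 and 128 reproduce. This is a minor, low-cost improvement in consistency.

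**What to change.** In Human factor evaluation, Questionnaires, insert baseline time in target glucose range into the covariate list directly after the baseline score. All three stratification factors are then in the model, as in the primary analysis.

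The cost is one phrase and one degree of freedom per model. No new data are needed: a run-in CGM record of at least 10 days with a time in range below 80% is required before randomisation, so every randomised participant has the value. The change should be made before the questionnaire data are analysed.

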#### Qualitative interviews

Data will be analysed thematically using the constant comparison method. NVivo, a qualitative software package, will be used to facilitate data coding/retrieval.

### Per-protocol analysis

A per-protocol analysis restricted to participants with a minimum of 60% CGM data during the control period and 60% use of closed-loop during the closed-loop period will be conducted for the primary endpoint.

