**Trial registration number:**

NCT05562492.

STRENGTHS AND LIMITATIONS OF THIS STUDYThe study adopts an open-label, multicentre, randomised parallel design.The study includes a 26-week follow-up period with equal numbers of study visits between both groups.The study includes young people (≥16 years) and adults with cystic fibrosis-related diabetes, including transplant recipients to support generalisability of the findings.The comparator therapy reflects the current standard of care and includes insulin injections or non-automated insulin pump therapy with continuous glucose monitoring.The study includes both quantitative and qualitative psychosocial evaluation.

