### Exclusion criteria

Any physical or psychological disease or condition likely to interfere with the normal conduct of the study or interpretation of study results as judged by the investigator.Commencement of CFTR modulator therapy within the previous 1 month.Previous solid organ transplant within the last 12 months or active on transplant waiting list.Use of closed-loop insulin therapy within the past 30 days.Known or suspected allergy to insulin.Severe visual impairment.Severe hearing impairment.Medically documented allergy or unable to tolerate the adhesive of plasters.Serious skin diseases at places of the body corresponding with CGM insertion sites.Participant is pregnant or breastfeeding or planning pregnancy within the next 12 months.

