### Standard insulin therapy with CGM group (control intervention)

Participants will use the Dexcom G6 CGM. Prior to starting the standard insulin therapy with CGM, participants will be trained on the use of the CGM. Written guidance will also be provided. Competency on the use of study CGM will be assessed. Participants will continue their standard insulin therapy with the study CGM for the next 26 weeks at home.

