### Visits during the 26-week home study period

Study visits will occur at 3 and 6 months following initiation of the respective study arm. These study visits will take place at the clinical research facility, outpatient department or remotely if preferred. The purpose of these visits is to review glucose data; to record any adverse events, device deficiencies and changes in insulin doses; and to document other medical conditions and changes in medications. Additionally, a participant’s body weight, height and FEV_1_ will be recorded. Participants will be asked to complete questionnaires to assess quality of life and diabetes management. Participants will have a blood test for HbA1c and complete a fasting (non-hypoglycaemic) C-peptide dried blood spot. At the end of the final study visit, study devices will be collected, and participants will resume their usual diabetes care.

Throughout the trial, clinical care will be provided by the local diabetes/CF teams as per usual care. Participants and/or the clinical team are free to adjust insulin therapy as per usual clinical practice, but no active treatment optimisation will be undertaken by the study team.

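### The per-protocol rule is worded for a crossover trial and sets delivery adherence in one arm only, so a control participant who starts closed-loop stays in the set and the direction of bias is unknown

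*Protocol article*

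**What the plan says.** The Per-protocol analysis section of the protocol article is one sentence. For the primary endpoint, the analysis is "restricted to participants with a minimum of 60% CGM data during the control period and 60% use of closed-loop during the closed-loop period". The section names no analysis model and no other condition for membership.

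Other parts of the article bear on it:

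- **Design.** The Overview describes a two-arm, single-period parallel trial.
- **Comparator.** The strengths and limitations box says that it is "insulin injections or non-automated insulin pump therapy with continuous glucose monitoring".
- **Control treatment.** The control-group section says: "Participants will continue their standard insulin therapy with the study CGM for the next 26 weeks at home". CGM wear is thus part of what controls are assigned.
- **Changes in therapy.** The section on visits during the home study period says: "Participants and/or the clinical team are free to adjust insulin therapy as per usual clinical practice".
- **Prior closed-loop.** The exclusion criterion is "Use of closed-loop insulin therapy within the past 30 days", which looks backwards from entry.
- **Withdrawal.** Significant protocol violation is listed among the possible reasons for withdrawal, at the investigator's discretion. Starting closed-loop is not named.
- **Primary analysis.** It includes all randomised participants by intention to treat. The model adjusts for baseline time in range, age and centre.

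**The concern.** There are three faults, all in a rule that the article itself states.

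1. **Wording.** The rule refers to a control period and a closed-loop period. In a parallel trial nobody has both, so read literally nobody meets both conditions.
2. **Asymmetry.** One arm is selected on use of the assigned insulin-delivery system and the other on availability of sensor data. Both are behaviours after randomisation, but they are not the same behaviour.
3. **Comparator not enforced.** A control participant who moves to closed-loop and keeps 60% CGM data satisfies the rule. Departing from the assigned treatment in this way is what a per-protocol set is meant to remove.

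At stake is whether this analysis can support or qualify the intention-to-treat result. If its bias has unknown sign, neither agreement nor disagreement with the primary analysis can be read with confidence.

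**Working it through.** **The plan's own figure.** Difference 5.0 points, SD 8.1, two-sided 5%, 90% power (Sample size calculation). The t-test calculation gives 56.13 per arm, rounded up to 57, or 114 in total, with power 0.904. Allowing for 10% loss, 57 / 0.90 = 63.3, rounded up to 64 per arm, or 128. The plan's figures reproduce, and the point does not affect them. The standard error of a difference at 57 per arm is 8.1 × √(2/57) = 1.52 points.

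**Who is in the set as written** (one criterion per arm):

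| Participant | CGM data | Closed-loop use | In the set? |
|---|---|---|---|
| Closed-loop arm | 70% | 50% | No |
| Control arm, stays on injections | 70% | none | Yes |
| Control arm, starts closed-loop | 70% | any | Yes |

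The third row contradicts the comparator definition. It needs no numerical assumption.

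**Effect A: retained control crossovers.** Let *c* be the fraction of controls who gain the full closed-loop effect for the whole period. The article gives no rate, so *c* is assumed. The expected difference is 5.0 × (1 − *c*):

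- *c* = 5%: 4.75 points, a loss of 0.25
- *c* = 10%: 4.50 points, a loss of 0.50
- *c* = 20%: 4.00 points, a loss of 1.00

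This moves the estimate toward no difference.

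**Effect B: the stricter filter in the closed-loop arm, with no true effect.** All inputs except the SD are assumed:

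- an engagement trait is worth *b* = 3 to 5 points of time in range per SD of the trait
- its correlation with device use is 0.6 in the closed-loop arm and 0.3 in the control arm
- the rule drops *f* = 10% to 25% of the closed-loop arm and 5% of the control arm

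Dropping the lowest fraction *q* of users raises the mean standardised use by k(*q*) = φ(z_q) / (1 − *q*). This gives k(0.05) = 0.1086, k(0.10) = 0.1950 and k(0.25) = 0.4237. The unadjusted shift is D = *b* × [0.6 k(*f*) − 0.3 k(0.05)]:

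- smallest (*b* = 3, *f* = 10%): 0.351 − 0.098 = 0.25 points
- largest (*b* = 5, *f* = 25%): 1.271 − 0.163 = 1.11 points

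Now add the baseline adjustment of the primary model. Suppose engagement acts equally at baseline and the correlation *r* between baseline and follow-up is 0.5 to 0.7 (also assumed). The arms then differ by D at baseline too, and the adjusted shift is about D × (1 − *r*):

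- smallest (*r* = 0.7): 0.253 × 0.3 = 0.08 points
- largest (*r* = 0.5): 1.108 × 0.5 = 0.55 points

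That is about 0.1 to 0.6 points toward closed-loop. If the control filter removed an equal share with equal correlation, the shift would be zero.

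**Both together**, with *c* from 5% to 20% and a true effect of 5.0 points:

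- with baseline adjustment: from 0.08 − 1.00 = −0.92 to 0.55 − 0.25 = +0.30 points
- without it: from 0.25 − 1.00 = −0.75 to 1.11 − 0.25 = +0.86 points

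The range covers zero either way.

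**The case against.** The strongest defence is that each arm is filtered on the device it was assigned, which is an ordinary per-protocol definition. CGM is part of the control treatment, so 60% CGM data is partly an adherence criterion there, and closed-loop cannot run without sensor readings. This stands in part: it is wrong to say that the control filter ignores adherence. But the control filter is silent on insulin delivery, which is the feature that separates the arms.

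A reader might infer that the set favours closed-loop and would show a benefit even with no true effect. The article does not support that. It gives no exclusion rate, no link between use and outcome and no crossover rate. The shift disappears under equal selection, and keeping control crossovers pulls the opposite way.

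A reader might also infer that the plan lets controls start closed-loop. It does not say so: controls are to continue their standard therapy, and the text on adjusting insulin does not mention closed-loop. No crossover is reported. What stands is that the stated rule would not remove such a participant, and withdrawal for protocol violation is only discretionary.

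Two further points are fair. A full protocol or SAP, not shown, may add further exclusions. Even so, the article fixes thresholds and wording that do not fit the design. Also, removing control crossovers is itself a one-arm exclusion after randomisation. That is a reason for cautious interpretation, but it does not justify counting them as per-protocol.

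**Conclusion.** The concern holds in limited form. It is certain from the text that the wording belongs to a crossover trial, that the criteria differ in kind between arms, and that a control participant on closed-loop would count as per-protocol. The sizes rest on assumptions: a dilution of 0.5 points of a true 5.0 for each 10% of controls who cross over fully, and a selection shift toward closed-loop of about 0.1 to 0.6 points with baseline adjustment, or up to about 1.1 without. The net sign is not determined. The largest selection shift, 1.11 points, is about 0.7 of the 1.52-point standard error. Severity is minor: the intention-to-treat primary analysis and the sample size are untouched.

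**What to change.** Amend the per-protocol definition before outcome data are analysed by arm:

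1. Replace *period* with *arm*.
2. Require at least 60% CGM data over the 26 weeks in both arms.
3. Define adherence to the assigned insulin-delivery method in each arm: at least 60% closed-loop use in the closed-loop arm, and no closed-loop use in the control arm.
4. State that the primary model, with its baseline adjustment, is used.
5. Report the number excluded by arm and reason, and describe the result as supportive and subject to selection after randomisation.

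This defines an analysis set only and changes nothing about what participants or care teams may do. A complier-average estimate could be added but should not replace the analysis. Participants below the 60% cut-off may still benefit from closed-loop, which breaks the assumption that assignment acts only through being above the cut-off.

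The cost is a few sentences and a little code. The Utility analysis already tabulates sensor time in both arms and closed-loop time in the closed-loop arm, so the only added item is a record of any closed-loop use among controls. The downside is a slightly smaller per-protocol set.
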